## Abstract

**Background:**

The evidence-based Dutch Obesity Intervention in Teenagers (DOiT) program is a school-based obesity prevention program for 12 to 14-year olds attending the first two years of prevocational education. This paper describes the study protocol applied to evaluate (a) the nationwide dissemination process of DOiT in the Netherlands, and (b) the relationship between quality of implementation and effectiveness during nationwide dissemination of the program in the Netherlands.

**Methods:**

In order to explore facilitating factors and barriers for dissemination of DOiT, we monitored the process of adoption, implementation and continuation of the DOiT program among 20 prevocational schools in the Netherlands. The study was an observational study using qualitative (i.e. semi-structured interviews) and quantitative methods (i.e. questionnaires and logbooks). Eight process indicators were assessed: recruitment, context, reach, dosage, fidelity, satisfaction, effectiveness and continuation. All teachers, students and parents involved in the implementation of the program were invited to participate in the study. As part of the process evaluation, a cluster-controlled trial with ten control schools was conducted to evaluate the effectiveness of the program on students’ anthropometry and energy balance-related behaviours and its association with quality of implementation.

**Discussion:**

The identified impeding and facilitating factors will contribute to an adjusted strategy promoting adoption, implementation and continuation of the DOiT program to ensure optimal use and, thereby, prevention of obesity in Dutch adolescents.

**Trial registration:**

Current Controlled Trials ISRCTN92755979.

## Background

How health-promotion programs perform, when widely disseminated under real-life conditions, has rarely evaluated [1]. Often, most effort is invested in assessing “efficacy”, i.e. the program’s effectiveness under well-controlled conditions [1,2]. The actual effectiveness of a health-promotion program depends on its efficacy, but also on its reach, adoption, implementation and maintenance [3-6]. However, when introduced under less-controlled conditions, insight into factors influencing the implementation of these efficacious interventions is crucial for translation into practice and systematic planning of dissemination strategies [7,8]. The aim of a dissemination strategy is to facilitate the process of behavioural change among implementers (e.g. professionals such as teachers, doctors, nurses), expected to be critical for the effective delivery of the program to the final target population (e.g. students, patients) [7]. Therefore, it is essential to tailor a dissemination plan to its users in order to stimulate applicability and transferability of health-promotion programs [7-9]. As yet, exemplary programs that have developed and evaluated effectiveness of a dissemination strategy in such a systematic way are scarce [3,10].

The Dutch Obesity Intervention in Teenagers (DOiT) program is an example of a health-promotion initiative that was ready for nationwide dissemination. DOiT is a school-based obesity prevention program for students attending the first two years of prevocational education (about 12–14 year olds). The DOiT program targets energy balance-related behaviours (EBRBs) in order to prevent overweight and obesity [11]. The program was developed using the Intervention Mapping (IM) protocol. Intervention Mapping is a protocol for developing health promotion interventions. Guided by six steps, the protocol supports intervention developers to identify and specify objectives, methods, and strategies regarding development, evaluation and implementation of interventions and programs [7].

DOiT showed promising effects on anthropometric measures (thinner skinfold thickness in girls and smaller waist circumference in boys) and EBRBs (a reduction in sugar-containing beverage consumption in both boys and girls and a reduction in screen-viewing time in boys) [12,13]. The accompanying process evaluation indicated that the majority of the students who were exposed to the program appreciated and used the DOiT materials and positively rated their experience with the program activities [14]. A majority of teachers regarded the DOiT materials as suitable for prevocational education. Teachers reported that they would recommend DOiT to other schools and planned to continue using DOiT themselves. Despite these positive findings, the evaluation exposed some impeding factors that hampered the implementation of DOiT. Most teachers needed more time than expected for the preparation and implementation of the lessons and they regarded the information contained in the materials to be too complex for the assumed student’s education level [14].

To prepare for wider dissemination in 2009, DOiT was adapted based on the teachers’ feedback from the former effect and process evaluation. A 7-step implementation strategy for DOiT was then developed in 2011 and a ‘DOiT support office’ was installed to guide and support the schools in their decision making, implementation and continuation with DOiT.

The objective of the described study was to evaluate the nationwide dissemination process of DOiT in order to gain insight into the facilitating factors and barriers to the nationwide dissemination of the DOiT program. Furthermore, the study aimed to evaluate the association between quality of implementation and effectiveness during the nationwide dissemination of the program in the Netherlands. We hypothesize that students attending schools with high quality of implementation will have better anthropometric and EBRBs outcomes, compared to students attending schools with lower quality of implementation. This article describes the study protocol applied for evaluation.

## Methods

Data collection took place between January 2011 and June 2013. Data analyses are planned to take place from September 2013 onwards. Figure 1 provides a flow chart of the study.

**Figure 1 F1:**
[figure not shown]
Flow chart of the DOiT study.

### Study design and population

The study was an observational study using qualitative (i.e. semi-structured interviews) and quantitative methods (i.e. questionnaires and logbooks), allowing data triangulation to evaluate the dissemination process of DOiT at 20 prevocational education schools in the Netherlands. As part of the process evaluation of the dissemination, a cluster-controlled designed study with ten control schools, matched on level of education, location (rural/urban area) and school size, was conducted to evaluate the effectiveness of implementation of DOiT on anthropometrics and EBRBs of adolescent students. Students were recruited via the schools, so no individual contact information was needed. At each school, three classes were invited to participate, i.e. all students and their parents. At least two weeks prior to the commencement of the study, parents and students received an information letter explaining the background, aim and procedures of the study. There were no individual inclusion or exclusion criteria for study participation. When students moved to another school, they were not included in the follow-up measurement.

The Medical Ethics Committee of the VU University Medical Center approved the study protocol in which we applied for a passive consent procedure for parents, students and teachers. A passive consent procedure means that students or parents who did not want to participate in the study could send a letter to the researcher should they choose to decline participation. Students who declined for participation were excluded from the measurements. The study protocol adhered to the RATS guidelines.

### Dissemination plan and intervention

Since January 2011, the DOiT program has been available for schools in the Netherlands. This implies that all schools in the Netherlands can select to buy the DOiT program. In order to reach Dutch prevocational schools, a project employee is posted in the DOiT support office, located at the VU University Medical Center. The DOiT support office stimulates the process of adoption, implementation and continuation of DOiT throughout the school year as well as updating the DOiT website and responding to feedback. The DOiT support office actively recruits schools by activities such as posting news items on relevant websites, or in digital mailings and being present at national conferences and local meetings of relevant stakeholders. Additionally, the DOiT support office informs prevocational schools by sending a DOiT introductory package consisting of an information letter with a factsheet, a brochure and exemplary teaching materials. All schools in the Netherlands have free access to the implementation strategy and accompanying materials on the DOiT website. This evaluation is, therefore, an integral part of the on-going ’real life’ dissemination process of DOiT throughout the Netherlands.

#### DOiT program

The program was developed according to the Intervention Mapping protocol [7] using input from representatives of the target group (adolescents), implementers (teachers) and parents. DOiT is a school-based obesity prevention program for 12 to 14-year olds. DOiT focuses on five EBRBs: (1) reducing intake of sugar-containing beverages; (2) reducing intake of high-energy snacks; (3) reducing screen time; (4) increasing levels of physical activity (i.e. active transport and sports participation) and (5) daily and healthy breakfast consumption [11]. The program consists of a classroom component, an environmental component and a parental component. The program covers 12 fixed theory lessons, four physical education (PE) lessons, equally divided over two school years, and three optional additional lessons. The classroom lessons in the first year aim to increase awareness and knowledge of EBRBs. The lessons in the second year focus on the influence of the (obesogenic) environment. The environmental component aims to raise awareness of the school environment, finding solutions to reduce negative influences within the environment and setting a plan for improvement. The parental component focuses on stimulating social support of the parents and raising awareness of the availability and accessibility of healthy products and activities in the home environment. As part of the DOiT program, all parents receive an information booklet in which the topics of the DOiT lessons are described. During the program, students receive homework assignments to complete with their parents. Optionally, at the end of the program schools can organize a meeting for parents, where students present what they learned.

The DOiT materials include a ’schoolbook’ accompanied by worksheets, a student toolkit (pedometer, food/exercise diary and an online computer-tailored advice) and a parental information booklet. DOiT is supported by an extensive teacher manual with a login for extra materials provided at the DOiT website. Table 1 provides an overview of the DOiT program.

**Table 1 T1:** Overview of the DOiT program

**Timeline**	**Classroom component**	**Environmental component**	**Parental component**
School year 1	**6 theory lessons:**		(1) Aimed at stimulating socialz support of the parents
	Aimed at raising awareness and information processing with regard to EBRBs		(2) Aimed at raising awareness of the availability and accessibility of healthy products and activities in the home environment
	**Materials:**		**Materials:**
	- 1 Textbook		- Information booklet
	- Online worksheets		- Homework assignments
	- Pedometer		- Information on DOiT website
	- Pocket-sized diary		- Optional parental meeting
	- Online computer-tailored advice		
	**2 PE lessons:**		
	Experiencing the acute effect of PA on the body measured by		
	(1) Pedometer		
	(2) Self-measured heart rate		
School year 2	**6 theory lessons:**	Aimed at raising awareness of the unhealthy environment, finding solutions and setting a plan for improvement of the environment	
	(1) Aimed at facilitation of choice to improve behaviour		
	(2) Aimed at raising awareness of the unhealthy environment, finding solutions and setting a plan for improvement of the environment	**Focus on:**	
		- Physical activity facilities in and around school	
		- Healthy school canteen	
		- (Un)healthy food retail outlets around school	
	**Materials:**		
			
			
	- 1 Textbook		
			
	- Online worksheets		
	- Small research		
	- Supportive video material		
	**2 PE lessons:**		
	(1) Experiencing the acute effect of PA on the body measured by self-measured heart rate		
	(2) Learn about sport possibilities in the neighbourhood		
Extra lessons	**3 optional additional lessons:**		
	(1) Cultural differences; learn about the cultural differences in food habits and physical activity		
	(2) Tasting; judging products by tasting, smelling and looking at (unfamiliar) snacks and soft drinks		
	(3) Cooking; preparing a healthy menu		

DOiT = Dutch Obesity Intervention in Teenagers; EBRB = Energy balance-related behaviour; PE = physical education; PA = physical activity.

#### Implementation strategy

Using the IM protocol, we developed the implementation strategy with the input of different implementation stakeholders. Teachers are the main implementers of DOiT. For that reason, teachers are supported by the DOiT implementation strategy. The strategy consists of seven steps to support adoption, implementation and continuation of DOiT within the school (see Table 2 for an overview). To facilitate the implementation process, a relatively low-profile implementation strategy with accompanying materials are available to teachers on the DOiT website [15]. The website provides general background information about the DOiT project, i.e. contact information, news items, information video, testimonials of schools who have successfully implemented DOiT, and a map of the Netherlands showing schools that currently implement DOiT. Teachers can read about DOiT and try the DOiT exemplary teaching materials in order to ensure that the program is compatible with their own context. The website has four domains targeting the different stakeholders i.e. 1) schools, 2) employees at supporting organisations, 3) parents and 4) students. In the parental domain, parents can read the information booklet online. Students have their own domain, containing a computer-tailored test and health-related videos. All domains are accessible free of charge.

**Table 2 T2:** Implementation strategy and materials for implementation of DOiT by teachers

**Dissemination phase**	**Implementation strategy**	**Accompanying materials**
Adoption	Step 1. Teacher reviews the DOiT program	DOiT factsheet, brochure and exemplary teaching materials
	Step 2. Teacher identifies barriers for implementation, identifies solutions and gains support within the school	Example presentation for colleagues and school management
Implementation	Step 3. Teacher decides to work with DOiT and develops a tailored plan for implementation	Implementation plan: a checklist
	Step 4. Teacher becomes familiar with the implementation of the program	Example email to inform colleagues about the start of DOiT
		Example time line for implementation
		Instruction video
		Teacher manual
	Step 5. Teacher delivers the program	Example presentation for parents
		Template of press release
		Teacher manual
Continuation	Step 6. Teacher concludes and evaluates the program	Teacher manual
		Manual for parent meeting
	Step 7. Teacher defines impeding and facilitating factors for implementation and creates a renewed plan for implementation and embedding of the DOiT program in the school	Evaluation form
		Advice for continuation

Due to the ’real life’ condition of the study, there was no teacher training, interference or guidance by the research team.

### Framework for evaluation

In order to systematically evaluate the process of implementation at the schools, eight process indicators were assessed: recruitment, context, reach, dosage, fidelity, satisfaction, effectiveness and continuation. These process indicators were derived from the Diffusion of Innovation Theory of Rogers [6], the model developed by Steckler and Linnan [16], the Process Evaluation Plan of Saunders [17] and the RE-AIM framework [4,18]. Table 3 presents the process indicators and their definition stratified for the dissemination phases.

**Table 3 T3:** Process evaluation indicators and their definition stratified for the three dissemination phases

**Process indicator**	**Definition**
**Adoption**	
Context	Factors of the physical, social, and political environment that either directly or indirectly affect the introduction of DOiT:
	a. Support within the schools (director and colleagues)
	b. School size; available budget; available hours for implementation of DOiT
	c. School environment (school canteen and sport facilities)
	d. Contamination with other programs aiming at a healthy lifestyle at school
	e. Teacher characteristics (e.g. knowledge, attitude, perception, willingness, self-efficacy, expectancy)
	f. Decision making process in the school
	g. Compatibility of the DOiT program with the regular curriculum
Recruitment	Exposure to sources and procedures applied for the recruitment of schools and teachers:
	a. Ways of approaching schools by the DOiT support office (used materials, message sent out)
	b. Ways of approaching schools by stakeholders (used materials, message sent out)
	c. Response of schools (reasons for agreement with participation, subgroups of recruited individuals or organisations, biases in response)
	d. Use of adoption materials
	e. Possible reasons for refusal or participation
Reach (1)	The extent to which the target population is reached by the recruitment strategy:
	a. Number of reached schools
	b. Number of reached stakeholders
**Implementation**	
Reach (2)	The extent to which the target population is reached by the implementation of DOiT:
	a. Number of teachers using DOiT
	b. Number of students using DOiT
	c. Number of parents reached by DOiT
Dosage	The proportion of DOiT lessons that were actually delivered or performed by the teachers and received by students:
	a. Implementation strategy activities that are accomplished
	b. Amount of DOiT lessons that are delivered or taught by teachers
	c. Completeness/delivery of implementation by the teachers (frequency, duration, mode of delivery, timing)
	d. Reasons for not delivering/implementing DOiT (facilitators/barriers for implementation)
Fidelity	The quality of the implementation of DOiT; the extent to which the teachers have implemented DOiT as intended by the developers:
	a. Compliance to the implementation strategy of DOiT (core elements)
	b. Compliance to the teacher manual of DOiT (core elements, standardisation)
Satisfaction	Subjective evaluation of DOiT and materials:
	a. General opinion about DOiT (by teachers, students and parents)
	b. Satisfaction with the DOiT program, materials, time spent and amount of lessons
	c. Satisfaction with implementation strategy, materials and support by DOiT support office
Effectiveness	The extent to which the DOiT program is effective:
	a. Behavioural and anthropometric change (students)
	b. Availability and accessibility of healthy products and activities in the home environment (parents)
	c. Availability and accessibility of foods and physical activity facilities in and around the school
**Continuation**	
Maintenance	The extent to which DOiT becomes routine and part of the curriculum and school policy:
	a. Embedding of DOiT in school health policy
	b. Embedding of DOiT in the curriculum of the school
	c. Future activities and intention to use DOiT
	d. Facilitators and barriers for future implementation

As part of the process evaluation, we assessed determinants that may explain the transition of the teachers through the subsequent stages of innovation: adoption, implementation and continuation. These determinants were categorized according to the innovation framework developed by Fleuren et al. [19]:

1) characteristics of the socio-political context, i.e. extent to which DOiT fitted into existing school health policy;

2) characteristics of the adopting organisation, i.e. decision making process in the school and school size;

3) characteristics of the teacher, i.e. teacher knowledge, skills, self-efficacy and intention to implement DOiT;

4) characteristics of the innovation, i.e. compatibility and flexibility of DOiT; and

5) characteristics of the dissemination strategy, i.e. training of the user and tools that influenced the implementation behaviour of the user.

The five determinant groups were operationalized into the process indicator context. The determinants will provide insight into factors that facilitate or impede the dissemination process of DOiT.

### Data collection procedures

#### Recruitment of schools

We aimed to include 20 DOiT implementation schools in the process evaluation. This number was based on feasibility and also a similar study, conducted in the Netherlands, evaluating the dissemination process of a Dutch healthy diet program, the Krachtvoer evaluation study [20].

After a school ordered the DOiT materials, the school was invited to participate in the study. The school was then informed about the study protocol by telephone and written information. If the school agreed to participate, the researcher visited the school in order to explain the procedures. Participating schools needed to meet the following criteria: (1) willing to implement DOiT during two subsequent school years; (2) a signed agreement of participation in the study during that period (2011–2013); (3) willingness to appoint a DOiT coordinator who was the linking agent between the research team and the school; (4) being able to participate with at least three classes of the first two years of their prevocational education, and (5) willingness to provide space and time for measurements. All teachers involved in the implementation of DOiT were asked to participate in the process evaluation. If schools participated in the study, they received free materials for three classes and a short report of the research results upon completion.

Regarding the process indicator effectiveness, 510 students per group were needed to detect a relevant difference in body mass index (BMI) between the intervention and control groups. Therefore, ten control schools were needed. Taking into account the clustered design, missing data and dropout (25%), a sample size of 1274 students were required to conduct multi-level analyses with an estimated power of 90% and an alpha level of significance set at 0.05 (see Table 4).

**Table 4 T4:** Number of subjects needed to detect a relevant difference between DOiT and control schools

**Outcome**	**sd**	**Difference**	**Number of subjects***	**Number of subject including 25% dropout**
BMI	1.2	0.25 kg/m^2^	510	637
Waist circumference	3.9	2 cm	80	100
Sum of skinfolds	14.6	5 mm	180	224
Sugar-containing beverages	840.4	250 ml/day	238	297
Sedentary behaviour	147.5	30 minutes/day	508	635
Active transport	23.3	10 minutes/day	115	143
Snacks	1.4	1 portion/day	40	51

*number of subjects required to conduct multi-level analyses with an estimated power of 90% and an alpha level of significance set at 0.05; sd = standard deviation based on the study of Singh et al. [12,13]; BMI = Body Mass Index.

In order to recruit control schools, we asked all intervention schools to provide the name of comparable schools in that area. As a result, we aimed to include control schools, matched on level of education, location (rural/urban area) and school size. Control schools did not implement DOiT during the study period. Regular contact with the management and teachers of control schools was ensured in order to promote their continued participation. Also the control schools received a short report of the research results upon completion.

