### Analyses

Our first aim is to evaluate the nationwide dissemination process of DOiT in the Netherlands All qualitative data systematically collected or observed during the study will be considered as data [29,30]. This means that not only information from in-depth interviews with teachers, but also all data reported during phone calls or observed during school visits will be included in the analysis. Regarding the interviews, a literal transcript of the audiotape of each interview will be written. All transcripts and other data will be marked with codes (open coding). The codes will be grouped into similar concepts in order to make them more workable, i.e. selective coding. Using tables and matrices, we aim to identify and compare facilitators and barriers around the key process indicators and implementation-related determinants. All quantitative data obtained from the logbooks and the teacher questionnaires collected during the study will be analysed in SPSS 20.0 (SPSS Inc. Chicago, Illinois, USA).

Our second study aim is to examine the relationship between quality of implementation and changes in students’ EBRBs and anthropometrics. The change in students’ EBRBs and anthropometrics will be analysed using multi-level linear regression analysis. We define three levels in our multi-level analyses: 1) student, 2) class, and 3) school. Analyses will be adjusted for baseline values, age, gender, ethnicity, and educational level. These variables will be checked as potential effect modifiers. Multilevel statistical analyses will be performed using MLwiN 2.22.

The process data, including information on level of dosage, level of fidelity and quality of delivery, will be combined into an ‘school implementation score’. Using linear regression analysis, we will examine the association between quality of implementation (implementation score) and program effect on EBRBs, as well as on anthropometrics. For all analyses a two-tailed significance level of <0.05 will be considered statistically significant.

In addition, we will explore the behavioural mediators of the intervention effect on BMI, waist circumference and sum of skinfolds using the product-of-coefficient method of MacKinnon [31]. We will specifically look at the mediating effects of consumption of sugar-containing beverages; consumption of high sugar/high fat snacks; sports participation; active transport; screen time and breakfast behaviour.

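### Table 4 is said to allow for clustering, but its numbers come from the two-sample formula for independent students, so the stated 90% power is unsupported

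*Protocol article*

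**What the plan says.** Under Recruitment of schools, the article sizes the effectiveness comparison on BMI: "510 students per group were needed to detect a relevant difference in body mass index (BMI) between the intervention and control groups". It continues: "Taking into account the clustered design, missing data and dropout (25%), a sample size of 1274 students were required to conduct multi-level analyses", with 90% power and alpha 0.05. Table 4 lists seven outcomes, each with a standard deviation, a difference, a number of subjects and that number including 25% dropout. The table footnote describes the column before dropout as the "number of subjects required to conduct multi-level analyses with an estimated power of 90% and an alpha level of significance set at 0.05". The Analyses section makes testing two-sided ("For all analyses a two-tailed significance level of <0.05 will be considered statistically significant") and sets out the model: "We define three levels in our multi-level analyses: 1) student, 2) class, and 3) school".

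The same sections give 20 intervention schools, 10 control schools and three invited classes per school. No ICC, design effect or number of students per school is given.

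**The concern.** Whole schools either use DOiT or do not, so the contrast is between schools and its precision depends heavily on there being only 30 of them, 10 in the control arm. The text and the table footnote both state that the numbers suit a multi-level analysis. If they were in fact calculated for independent students, the planned model will include between-school variance that the sample size left out.

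The rows at risk are BMI and sedentary behaviour, which need 510 and 508 students per group and so drive the sample size. Waist circumference and snacks need far fewer and have ample margin. At stake is the reading of a null result on BMI or sedentary behaviour: a reader relying on the stated 90% would take it as stronger evidence of no effect than the design can give.

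The point is not that an ICC is unreported, which a condensed article may leave to the full protocol. The article makes a positive claim that its own table contradicts.

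**Working it through.** **Step 1: reproduce Table 4.** Inputs are the printed standard deviations and differences, two-sided alpha 0.05 and 90% power. For independent individuals in two equal groups:

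n per group = 2 × (1.960 + 1.282)² × sd² / difference² = 21.015 × sd² / difference²

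| Outcome | sd | Difference | Formula, no clustering | Stated | Stated / formula |
|---|---|---|---|---|---|
| BMI | 1.2 | 0.25 | 484.2 | 510 | 1.053 |
| Waist circumference | 3.9 | 2 | 79.9 | 80 | 1.001 |
| Sum of skinfolds | 14.6 | 5 | 179.2 | 180 | 1.005 |
| Sugar-containing beverages | 840.4 | 250 | 237.5 | 238 | 1.002 |
| Sedentary behaviour | 147.5 | 30 | 508.0 | 508 | 1.000 |
| Active transport | 23.3 | 10 | 114.1 | 115 | 1.008 |
| Snacks | 1.4 | 1 | 41.2 | 40 | 0.971 |

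Five rows agree within 1%. Snacks lies slightly below the formula, whereas a design effect above 1 would raise it.

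**Step 2: the BMI row.** An sd of 1.232, which prints as 1.2, gives 510. Any sd from 1.15 to 1.25 prints that way and gives about 445 to 526. If the excess were instead a design effect of 1.053, then from 1 + (m − 1) × ICC the implied ICC would be 0.053 / 50 ≈ 0.001 at 51 students per control school (510 / 10), or 0.053 / 33 ≈ 0.0016 at 34 per school (1020 / 30). A design effect in this row alone is implausible when sedentary behaviour, with almost the same n, has none.

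**Step 3: the remaining steps.** 510 × 1.25 = 637.5 (stated 637), and 2 × 637 = 1274. The table labels the first step as dropout, and the second adds the two groups.

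**Step 4: power with clustering.** The ICC and the students per school are assumptions. For BMI (sd 1.2, difference 0.25), with m students analysed per school:

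variance = sd² × [(1 + (m_c − 1) × ICC) / n_c + (1 + (m_i − 1) × ICC) / n_i]

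Power comes from the non-central t distribution with 30 − 2 = 28 degrees of freedom.

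- Layout A: 510 against 510 analysed, so 51 per control school and 25.5 per intervention school.
- Layout B: equal numbers per school after 25% loss. Control 637 × 0.75 ≈ 478 and intervention 2 × 478 = 956, so 47.8 per school.

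Example, layout A at ICC 0.02: variance = 1.44 × (2.00 + 1.49) / 510 = 0.00985. The standard error is 0.0993, 0.25 / 0.0993 = 2.52, and power is 68%.

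| ICC (assumed) | Design effect at 51 per school | Power, A | Power, B | BMI difference detectable at 90% power, B |
|---|---|---|---|---|
| 0.005 | 1.25 | 84% | 90% | 0.25 |
| 0.01 | 1.5 | 78% | 84% | 0.27 |
| 0.02 | 2.0 | 68% | 73% | 0.31 |
| 0.03 | 2.5 | 60% | 64% | 0.35 |
| 0.05 | 3.5 | 48% | 50% | 0.41 |

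Sedentary behaviour (sd 147.5, difference 30) is slightly worse in layout A: 76%, 66% and 46% at ICC 0.01, 0.02 and 0.05.

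**The case against.** The strongest reply concerns the size of the shortfall. The loss depends on an ICC that the article does not give. The relevant ICC is that of the outcome adjusted for baseline, age, gender, ethnicity and educational level, which may be smaller than a crude one. Inviting three classes at each of 20 intervention and 10 control schools points towards layout B, where power is about 95% at ICC 0, 93% at 0.002 and 90% at 0.005. This stands as a limit on the claim: the plan does not fail at every ICC. But layout B keeps 90% only up to about 0.005, and only through extra intervention students. It implies about 637 + 1274 = 1911 enrolled, not the 1274 the article says is required.

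The match is also not exact in every row. BMI, which sets the sample size, is 5% above the formula, and the rounding explanation is inferred because the source data are not at hand. Even so, the alternative reading leaves an allowance for clustering close to nothing.

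The planned three-level model does handle clustering, so the effect analysis is not invalid on this account. That is correct, but the model does not supply the power that the sample size claims.

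Finally, effectiveness is one of eight process indicators, the 20 intervention schools were chosen partly on feasibility, and data collection ended in June 2013. This limits what can be changed, but the power statement can still be corrected.

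**Conclusion.** The concern holds. The statement that the sample size allows for the clustered design is contradicted by Table 4, which contains no meaningful design effect: six rows match the unclustered formula within 3%, and the seventh does so once rounding of its sd is allowed for. This follows from the article's own figures and needs no assumption about the ICC.

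The 90% power is therefore unsupported for BMI and sedentary behaviour. How far it falls short rests on an assumed ICC. Over 0.01 to 0.05, BMI power is 78% down to 48% with 510 analysed per group, and 84% down to 50% in the more favourable layout. In that layout the detectable BMI difference rises from the planned 0.25 to between 0.27 and 0.41 kg/m². Below an ICC of about 0.005 the favourable layout would still reach 90%, but the article neither states such a value nor counts the students it would take.

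**What to change.** Either remove the clause claiming that the clustered design was taken into account, together with the footnote's reference to multi-level analyses, or recalculate Table 4 with the design effect 1 + (m − 1) × ICC. A recalculation should state the ICC, for example as estimated from the earlier DOiT trial data that supplied the standard deviations, and the students per school.

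Because the number of schools is fixed, replace the 90% for BMI and sedentary behaviour with the power, or the difference detectable at 90% power, for 10 control and 20 intervention schools over a stated ICC range. State that null results on these outcomes will be interpreted through confidence intervals.

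The cost is rewording and one recalculation. The stated power becomes less favourable. No extra students or schools are needed, and with analyses planned from September 2013 onwards the correction concerns only how the results are presented and read.
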